### Randomization

Randomization of each participant to one of the three feedback conditions will be carried out using a computer-generated random number list with a blocked randomization scheme (block size 6, randomization ratio [1:1:1]). An independent researcher will allocate the participants to the feedback conditions after the baseline assessment. To ensure that the distribution of parents and children and adolescents is similar across the three feedback conditions, randomization will be stratified by age of the child or adolescent (4 to 11 years old and 12 to 17 years old). To exclude confounding due to differences among departments, randomization will also be stratified by department (Arnhem, Ede, Nijmegen and Tiel).

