### Participants

The study will take place in all of Pro Persona’s outpatient youth departments (in Arnhem, Ede, Nijmegen and Tiel). Pro Persona is a specialised mental health care institution in the Netherlands that offers outpatient and inpatient treatment for children, adolescents, adults and the elderly. Approximately 110 clinicians work in the outpatient youth departments. These clinicians are social workers, social psychiatric nurses, nurse practitioners, educationists, psychologists, health care psychologists (GZ-psychologen), clinical psychologists, psychiatrists and physicians.

All families with children and adolescents between the ages of 4 and 17 years who are referred to Pro Persona’s outpatient youth departments receive information about the study. We will include children and adolescents with any kind of mental health problems (e.g. developmental, anxiety or mood disorders) and any kind of treatment (e.g. individual or group treatment, cognitive-behavioural or solution-focused treatment, frequent or irregular treatment). On average, 33% of the treatments in youth mental health care last less than 3 months, 35% last from 3 to 12 months and 31% last more than a year
[47]. The only exclusion criterion will be child’s, adolescent’s or parent’s insufficient understanding of the Dutch language. If the child is between 4 and 11 years old, the parents will be approached to participate in the study, because younger children are less able to fill out questionnaires and parents are legally responsible for the children. If the child or adolescent is between 12 and 17 years old, the child or adolescent will be approached to participate in the study. Children and adolescents under 16 years of age will only be approached to participate after parental consent for participation in the study is obtained. Children, adolescents and parents who agree to participate will sign an informed consent form. Participants will be randomly allocated to one of the three feedback conditions (144 participants per condition), using a block randomization scheme. Randomization will be carried out by an independent researcher after the baseline assessment.

We are aware that prior research has shown systematic discrepancies between multiple informants with regard to the nature and severity of children’s and adolescents’ symptoms

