In addition to the procedure in the second feedback condition, clinicians in the third feedback condition will discuss the feedback with a colleague. In order to structure the discussion, clinicians will be given a standardized format for case consultation. They will be required to complete the format and return it to the researcher. Thus, clinicians will be obliged to pay attention to the feedback and will receive additional advice from their colleagues about ways to improve treatment.

In all of the conditions, we will monitor whether clinicians actually discuss the feedback with their clients by asking children, adolescents and parents within the standard set of questionnaires. In the third feedback condition, we will also monitor whether clinicians actually discuss the feedback with a colleague. After all, if clinicians do not use feedback constructively, it is unlikely that outcomes will improve.

Before the start of the trial, all clinicians of the participating youth departments will be trained to interpret the feedback, discuss the feedback with clients and use the standardized format for case consultation with a colleague. Besides that, a ROM-implementation package with various kinds of tools has been developed to help clinicians with ROM and use of the feedback. In addition, a helpdesk will be available for children, adolescents, parents and clinicians.

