A limitation of the study is that differences in the care provided to participants in the second and third feedback conditions other than the intervention can arise (performance bias), because the intervention will be focused on the clinician. Since clinicians will not be blinded, it is possible that they will make additional efforts to improve treatment outcome when they receive feedback reports from the second and third feedback conditions instead of the first condition (control condition). Besides that, it is possible that effects from the third feedback condition will spill over to the second feedback condition. If clinicians have discussed several feedback reports with their colleagues (third feedback condition), they might guess what reactions their colleagues would have and what advice they would offer for clients who are not discussed (second feedback condition). Because each clinician will only have a couple of clients in each feedback condition, we think that such a spillover effect is unlikely. Furthermore, clients in the second and third feedback conditions may experience a placebo effect if their clinicians reveal that their feedback reports are being discussed with a colleague to improve treatment. In addition, due to technical and logistic restrictions, we are unable to check whether clinicians actually discuss the feedback with the children, adolescents and parents. However, we will remind the clinicians to discuss the feedback by sending them e-mail messages and we will ask clients at each measurement whether the feedback was discussed. Lastly, due to financial constraints, we will be unable to investigate the long-term effects of feedback in youth mental health care. Hence, further research should include follow-up measurements after treatment has ended.

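### A single published block size of 6 in an unblinded trial makes up to 20% of assignments foreseeable to a fully informed observer; undisclosed varying block sizes would cut that ceiling at almost no cost

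*Protocol article*

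**What the plan says.** The Randomization section specifies allocation "using a computer-generated random number list with a blocked randomization scheme (block size 6, randomization ratio [1:1:1"). Two stratification factors apply: "randomization will be stratified by age of the child or adolescent (4 to 11 years old and 12 to 17 years old") and "randomization will also be stratified by department (Arnhem, Ede, Nijmegen and Tiel"). That makes 2 × 4 = 8 separate lists. On concealment it says "An independent researcher will allocate the participants to the feedback conditions after the baseline assessment".

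Strengths and limitations acknowledges the lack of blinding: "Since clinicians will not be blinded, it is possible that they will make additional efforts to improve treatment outcome". It goes on to discuss performance bias, spillover and placebo effects, but not predictable allocation.

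Under Intervention, conditions 2 and 3 receive the same report content. Condition 3 adds a structured discussion with a colleague, and of the consultation form it says of clinicians "They will be required to complete the format and return it to the researcher". Participants gives the staffing: "Approximately 110 clinicians work in the outpatient youth departments".

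**The concern.** With one fixed block size at 1:1:1, each block of six contains exactly two clients per condition. Someone who knows the size and the earlier allocations in a stratum can work out what is left, and late in a block the next assignment may be certain. An independent researcher holding the list conceals the list, but does not prevent this inference from allocations already revealed.

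Earlier allocations become partly visible here. Reports are filed in the electronic patient record, the reports for conditions 2 and 3 carry extra content, and a colleague takes part in each condition 3 case. Condition 3 also gives the clinician extra work, and the Background lists administrative pressure, caseload and lack of time as barriers to using feedback. A wish to avoid condition 3 for some clients is therefore conceivable.

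If consent, completion of baseline or the timing of entry responded to a guessed allocation, the conditions could differ in case mix before treatment. The planned adjustment covers only measured covariates found to differ between groups, so selection on unmeasured prognosis or motivation would remain.

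**Working it through.** **The plan's own figures.** The plan states no predictability figure. Its sample size reproduces: noncentral F with f = 0.15, 3 groups, 3 covariates and α = 0.05 gives N = 432 (power 0.801), and 432/(1 − 0.5) = 864. Mean stratum size is 432/8 = 54 (9 blocks) to 864/8 = 108 (18 blocks).

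**Ceiling: an observer who knows all earlier allocations in the stratum and the block boundaries** (block of 6, 2:2:2, 90 orderings).
- Next assignment certain: the 6th always; the 5th when the last two share a condition, probability 1/5. Share = (1 + 0.2)/6 = 20%.
- Condition 3 already used up after k assignments: C(k,2)/15. For k = 0 to 5 this is 0, 0, 1/15, 3/15, 6/15, 10/15. Share = (20/15)/6 = 22.2%.
- At least one condition ruled out, by position: 0, 0, 0.2, 0.6, 1, 1. Share = 2.8/6 = 46.7%.
- Best-guess accuracy by position: 0.333, 0.400, 0.500, 0.533, 0.600, 1.000. Mean 56.1%, against 33.3% by chance.

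**Reports only.** Reports separate condition 1 from conditions 2/3, but not 2 from 3. The next condition is certain only when all four condition 2/3 places are used, so that only condition 1 remains. This happens at the 6th place with probability 1/3 and at the 5th with probability 1/15. Share = (1/3 + 1/15)/6 = 6.7%. Condition 3 can be ruled out for the same 6.7%.

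**Partial sight.** Suppose each earlier allocation is known independently with probability q (an assumption; the plan gives no value). Certainty requires that all four places of the other two conditions have been seen, so the share is 0.2 × q⁴.

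| q | Certain share |
|---|---|
| 1 | 20% |
| 0.9 | 13.1% |
| 0.75 | 6.3% |
| 0.5 | 1.25% |
| 0.25 | 0.08% |
| 1/27.5 | practically 0 |

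The last row is one clinician seeing only their own clients, with 110/4 = 27.5 clinicians per department on average.

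**Varying sizes.** Simulation with equally likely sizes and 108 clients per stratum; the observer sees everything earlier and knows the set of sizes but not their order. The sets are assumptions, since the plan names no alternative.

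| Sizes | Certain | Best guess correct |
|---|---|---|
| 6 (fixed, exact) | 20% | 56.1% |
| 3, 6 | 8.6% | 57.7% |
| 6, 9 | 4.9% | 54.1% |
| 6, 9, 12 | 2.3% to 2.5% (repeated runs) | 53% |

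With 6, 9 and 12, condition 3 can be ruled out for about 3% of assignments instead of 22%.

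**The case against.** The strongest reply is that the procedure is conventional and well protected. The list is computer-generated, an independent researcher allocates, and consent and a web-based baseline come first. All referred families are approached, and there is one exclusion criterion. Nothing in the article says that clinicians recruit, judge language ability or control the order of entry. To steer a client, a clinician would have to time a family's online questionnaire against entries from every colleague in the stratum. The motive is inferred, not documented. All of this stands: it makes bias a possibility, not a finding.

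Four stronger readings are tempting, and the document does not support them.
- A reader might infer that one assignment in five will in practice be known. Apart from the independent researcher, the article describes nobody with complete sight of a stratum, and each clinician has very few clients per condition.
- A reader might infer that the report reveals the condition. It does not separate condition 2 from 3. The consultation reveals condition 3 to the clinician and a colleague; the article does not say that the whole department learns of it. About half of participants are expected to stop after baseline, which further limits what reports during treatment can show.
- A reader might call the strata small. The mean is 54 to 108 clients, and the 20% does not depend on stratum size.
- A reader might expect varying sizes to remove the problem. They remove most certainty but little guessability, and sizes 3 and 6 would slightly raise best-guess accuracy.

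The reply does not remove the stated choice itself: one size, fixed and printed, where clinicians are unblinded.

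**Conclusion.** The point holds as a minor design weakness. The 20% (certain) and 22% (condition 3 ruled out) are exact but are ceilings: they assume complete knowledge of earlier allocations and block boundaries within a stratum. Under more plausible sight the certain share ranges from about 6.7% or 6.3% (reports alone, or three quarters of allocations known) to practically zero for a single clinician. The partial-sight figures assume that allocations are seen independently, and the single-clinician figure assumes equal caseloads and departments of equal size.

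A reader might conclude that the comparison is already biased. The article gives no evidence of that, and sample size and power are unaffected. The case for change rests on its very low cost.

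**What to change.** In the Randomization section, have the independent researcher generate the same stratified 1:1:1 list with randomly varying block sizes that are multiples of 3, for example 6, 9 and 12. Withhold the sizes and their order from the departments and the study team until the last client is allocated. Avoid the pair 3 and 6, which gains less on certainty and nothing on guessing. If the trial has started, apply the change to the unused part of each stratum's list.

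The cost is regenerating one computer list. The worst-case difference between two conditions from an incomplete last block rises from 2 to 4 clients per stratum (a block of 12 holds four per condition), which is negligible at a mean of 54 to 108 clients per stratum.

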### Statistical analyses

All analyses will be conducted using Mplus
[64], because this program allows analyses of complex data while taking into account the longitudinal character of the data. Intervention effects will be analyzed according to the intention-to-treat principle and the completers-only framework. For the intention-to-treat analysis, missing data will be handled using multiple imputations (MI). Descriptive statistics will be calculated for all variables of interest (e.g. symptoms, quality of life, satisfaction with treatment, number of sessions, length of treatment, dropout rate). In order to assess whether randomization resulted in equal groups, we will examine whether there are differences among the three feedback groups on relevant covariates (e.g. sex, age, educational level, ethnicity, socioeconomic status, marital status, household composition and diagnosis) using ANOVA for the continuous variables and Chi-Square tests for the categorical variables. Variables that are distributed differently among the three groups will be entered as control variables in all models testing the effects of the feedback conditions. The hypotheses will be tested using multivariate linear regression analyses. In addition, we will examine whether being NOT moderates the association between the feedback intervention and symptom severity. Therefore, interaction terms will be calculated as the product of the feedback condition and whether or not the client is NOT. These terms will be added as a second step in the multivariate analyses. Reporting of the results of the study will be in accordance with the CONSORT statement
[65,66].

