### Sample size calculation

Literature indicates various effect sizes of feedback from ROM
[17,21,27,62]. The present study was powered to detect the upper limit of a small effect size (f = 0.15; ANCOVA). A power analysis using G*Power
[63] indicated that a total sample size of 432 (n = 144 per condition) would be sufficient to detect significant (α = .05, power = .80) condition effects on symptom severity (3 conditions, including testing for 3 covariates and possible interaction effects).

However, our previous experiences have shown that approximately 50% of the participants stop filling out questionnaires after one measurement (baseline assessment). Hence, the clinicians of these children, adolescents and parents do not receive feedback during treatment. It would not be desirable to impute 50% of the data as this would make the imputation highly unreliable. Therefore, we will invite twice as many children, adolescents and parents (n = 288 per condition and 864 in total) to include the required number of 144 participants per condition of whom clinicians have received feedback during treatment (i.e. at least 50% of the measurements).

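### Control variables are picked by baseline difference tests instead of being fixed in advance, so the primary model depends on chance and gives up precision

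*Protocol article*

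**What the plan says.** Under Statistical analyses, the article tests the three arms for baseline differences, using ANOVA for continuous and Chi-Square tests for categorical variables. It gives eight examples, running from sex and age to household composition and diagnosis. The consequence is stated as a rule: "Variables that are distributed differently among the three groups will be entered as control variables in all models". No significance level is given for calling a variable differently distributed. The hypotheses are then tested by multivariate linear regression.

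Under Sample size calculation, the trial is "powered to detect the upper limit of a small effect size (f = 0.15; ANCOVA"), with "α = .05, power = .80", for "3 conditions, including testing for 3 covariates and possible interaction effects". The three covariates are not named.

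Under Randomization, "randomization will be stratified by age of the child or adolescent (4 to 11 years old and 12 to 17 years old"), and "randomization will also be stratified by department (Arnhem, Ede, Nijmegen and Tiel"). Allocation follows the baseline assessment, so baseline SDQ and both strata are known for every participant before an arm is assigned. Age group also decides who completes the SDQ: the parent at 4 to 11 years, the child or adolescent at 12 to 17.

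**The concern.** With a computer-generated list run by an independent researcher, any baseline difference between the randomised arms is chance. A test for such a difference says nothing about whether the variable predicts outcome, and prediction of outcome is what makes a covariate worth having.

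The rule also works against the design. Stratified blocks keep age group and department nearly equal across arms, so an imbalance test will rarely select them. Yet age group carries the change of informant, and the Participants section itself acknowledges systematic disagreement between informants. If the strata stay out of the model, the variance they explain remains in the error term and standard errors are on average too large.

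Baseline SDQ total difficulties is plausibly the best single predictor of later SDQ, and the text on adjustment does not mention it. At stake are the precision of the primary comparison and whether its model is settled before the data are seen. The rule covers all effect models, so the secondary outcomes are affected too.

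**Working it through.** **Inputs from the article.** f = 0.15; alpha 0.05; power 0.80; three arms; three covariates; N = 432; eight example variables for the baseline tests; block size 6; two age groups by four departments, which is 8 strata.

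**Assumed, because the article does not give them.** The correlation r between baseline and outcome SDQ (0.3 to 0.7 shown); a 5% level for the baseline tests; independence of those tests.

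**1. The article's own figure.** Omnibus F test with numerator df = 3 − 1 = 2, denominator df = 432 − 3 − 3 = 426 and noncentrality λ = f²N = 0.15² × 432 = 9.72. Power is 0.8007, so 432 reproduces. With no covariates (denominator df 429) power is 0.8008 and the required N is again 432. The three covariates therefore cost only degrees of freedom, and no explicit gain from explained variance was built in.

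**2. If f = 0.15 is on the covariate-adjusted scale and baseline SDQ is left out.** The effective size is f × √(1 − r²); for r = 0.5 this is 0.15 × √0.75 = 0.1299, and λ = 7.29.

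| r | effective f | power at N = 432 | N for 80% |
|---|---|---|---|
| 0.3 | 0.1431 | 76% | 474 |
| 0.5 | 0.1299 | 67% | 574 |
| 0.6 | 0.1200 | 60% | 673 |
| 0.7 | 0.1071 | 50% | 843 |

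**3. If f = 0.15 is on the raw scale.** The unadjusted analysis keeps 80%. Adjustment raises the effective size to f / √(1 − r²).

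| r | effective f | power at N = 432 with baseline |
|---|---|---|
| 0.3 | 0.1572 | 84% |
| 0.5 | 0.1732 | 91% |
| 0.6 | 0.1875 | 95% |
| 0.7 | 0.2100 | 98% |

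**4. What the rule itself would do if baseline SDQ were among the tested variables.** Simulation, 4,000 runs per setting, f on the adjusted scale, baseline entered only when it differs at p < 0.05:

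| r | power, no adjustment | power, rule | power, fixed ANCOVA | type I error, rule |
|---|---|---|---|---|
| 0.5 | 66% | 67% | 80% | 4.7% |
| 0.6 | 59% | 59% | 79% | 3.6% |
| 0.7 | 50% | 51% | 80% | 3.4% |

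The rule lets baseline in about 5% of the time, so it performs almost like no adjustment. Its type I error is at or below the nominal 5%.

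**5. How often chance alone changes the model.** Eight independent tests at 0.05 give 1 − 0.95⁸ = 0.337, about 34% for at least one false flag. The named variables are likely to be correlated, so this is indicative only.

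**6. Balance of the strata.** A block of 6 holds two places per arm, so within a stratum two arms can differ by at most 2. Over four departments an age group can differ between arms by at most 8 among those randomised. A test on age group will seldom flag it.

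**The case against.** The strongest reply is that the text says less than a critic might read into it.

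- A reader might infer that baseline SDQ can never enter the model. The article does not support that. The tested variables are introduced as examples, and Mplus is chosen partly because it handles the longitudinal structure, so baseline SDQ could enter as a repeated measure.
- A reader might infer that no covariate is fixed at all. The sample size section mentions three, and the imbalance rule could be an addition to them. A full analysis plan, not shown, may name them.
- A reader might infer that the trial is underpowered. Since 432 also results with no covariates, a shortfall against 80% follows only if f = 0.15 is meant on the adjusted scale, which the article does not say.
- A reader might infer a false-positive risk. The simulation shows none, and omitting stratification factors errs on the conservative side.

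All four limits stand. They do not remove the point, because the selection rule is stated explicitly and is not a detail left for later. If baseline SDQ is on the tested list, the rule admits it only about one time in twenty. If other covariates are fixed, the rule still lets chance differences alter every effect model. Attrition might also unbalance the analysed participants in ways that are not chance, but the article presents these tests as a check on the randomisation, and prespecified prognostic covariates would serve that purpose better.

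**Conclusion.** The point holds as a fault in a stated rule: control variables are selected by chance imbalance, the selection tends to pass over the stratification factors, and it does not match the ANCOVA with three unnamed covariates used for the sample size.

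The harm is lost precision and a primary model that depends on the data. Its size turns on the unknown r and on the scale of f: either power below the stated 80% (adjusted scale) or a gain forgone above it (raw scale). The sample size of 432 is not itself wrong. This should be fixed as a free improvement; it does not threaten the validity of the trial.

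**What to change.** Delete the imbalance-driven rule. Prespecify the primary model with condition, baseline SDQ total difficulties, age group (informant) and department as fixed terms. For secondary outcomes, use the same strata plus the baseline value where one exists; quality of life has one, while satisfaction, sessions, length of treatment and dropout do not. Name the three covariates in the sample size section, or change that number so that it agrees with the model, and say which scale f = 0.15 is on. Letting the baseline slope differ by informant is optional. Baseline characteristics can still be tabulated by arm, without using tests to choose covariates.

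The cost is one paragraph. Every variable is already recorded before allocation, and the extra degrees of freedom are negligible: with N = 432, power is 0.8008 with no covariates and 0.8007 with three.
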